### Objectives of the Study and Hypotheses

The ambition of our study is to investigate both the effectiveness of a VR gait training program (using a VR-HMD) and the acceptance of the VR device among healthy older adults. The effectiveness of the VR gait training program will be compared with that of a conventional training program of NW. The choice to compare a VR gait training program method to NW reflects the ambition of this work. From our point of view, NW offers the ecological context that is most conducive to the maintenance and even improvement of the functional relationships between perception and action. The walker must constantly adjust locomotion parameters in reference to obstacles to produce adaptive behavior in cluttered environments. Our VR gait training program aims to be the counterpart of NW in a perfectly controlled context thanks to VR technologies. Demonstrating the potential of our protocol would seem more convincing to us if it were established that the improvements induced by using a VR device were equivalent or even superior to those induced *via* NW. The comparison of the gait training programs’ effectiveness will be based on a pre- and postintervention comparison of gait adaptability capacity improvements based on further levels of analyses (as presented earlier). The 2 gait training programs will be offered to healthy older adults (with no fall history) with a systemic approach to fall prevention intended to avoid or at least delay the first fall occurrence. The study of VR-HMD acceptance will be based on the Technology Acceptance Model (TAM) [54-56].

The VR gait training program will be implemented following the different guidelines presented earlier. On the basis of all the previous precautions, our future gait training program in fully immersive VR may potentially improve both functional and psychological outcomes. We hypothesize that both gait training programs will lead to improvements in gait adaptability behavior capacities (hypothesis 1) but that the VR gait training program will induce greater improvements in gait adaptability capacities in comparison with the NW training (hypothesis 2). Finally, we hypothesize that older adults will accept the VR-HMD before the VR gait training program (hypothesis 3) but that acceptance will increase throughout the gait training program (hypothesis 4).

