In summary, our software will allow us to implement the main principles of Hendry et al [45] presented in the introduction. The VR training program was designed in particular to optimize the variability of the practice conditions and to allow the learner to have qualitative feedback on the success of the task. The variability of the practice conditions was obtained essentially by manipulating the location of the obstacles, their dimensions, and the nature of the task. The speed of locomotion was not manipulated as such, given that participants were asked for each trial to complete the route as quickly as possible while giving priority to precision. Concerning feedback, at the end of each trial, the participant will have the possibility of requesting feedback related to the knowledge of result (self-controlled feedback). It has been shown that this type of feedback makes it possible to enhance learning by placing the participant at the heart of the learning experience and developing their autonomy [69-71]. One of the main advantages of the self-controlled feedback procedure is that it allows participants to use feedback to optimize control processes without inducing a dependency effect. Indeed, the literature indicates that participants spontaneously implement a fading procedure [71] by requesting feedback massively at the start of the training period and then less often, which protects them from any dependence on feedback [50].

A stratified randomization (with the sex factor) will be conducted, using a computer software program to generate a random sequence. Two strata (male and female) will be identified, and randomization will be applied to each stratum. For instance, when a male older adult participates in the study, he will be the first to be allocated to the male strata, and the group (VR group and NW group) will be determined through randomization applied to the male stratum.

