#### Sample Size

The sample size calculation was performed using G*Power (version 3.1.9.7). To detect relevant within-between-group differences, we calculated a sample size sufficient to detect small effect sizes. On the basis of values generally observed in studies conducted in the field of acceptability and acceptance of technologies in general (because no study similar to ours has yet been conducted), f=0.2, α=.05, and *P*=.80 were chosen to favor clinically significant effect sizes [79]. To test the main hypotheses of this study, 50 participants are required. To compensate for possible dropouts, 5 more participants will be included in each group. The 2 groups will be composed of 30 participants each.

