#### Statistical Analysis

The statistical software JASP (version 0.17.1; 2023) will be used to run statistical analyses. The statistical level of significance was set at α=.05. Nonparametric tests were used when the distribution of the data was nonnormal. The statistical analysis will allow us to determine the effects of the two different training programs on the primary and secondary variables. The analysis will include participants who completed all the pretests and the posttests. Adherence to programs will be measured by the absence rate (in terms of %). Comparisons within and between groups before and after the intervention will be done using repeated measures ANOVA and Tukey tests as post hoc analyses. Effect sizes will be calculated using partial η^2^.

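### Hypothesis 2 is better tested by one planned VR-minus-NW contrast at T1, adjusted for T0 and sex, than by an unnamed term of a repeated measures ANOVA with Tukey follow-up

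*Protocol article*

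**What the plan says.** The Objectives of the Study and Hypotheses section predicts that "the VR gait training program will induce greater improvements in gait adaptability capacities in comparison with the NW training (hypothesis 2"). It bases the evaluation on a "pre- and postintervention comparison of gait adaptability capacity improvements". The target is therefore a difference between groups in change.

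The Statistical Analysis section answers with: "Comparisons within and between groups before and after the intervention will be done using repeated measures ANOVA and Tukey tests as post hoc analyses". It adds "Effect sizes will be calculated using partial η^2", "The statistical level of significance was set at α=.05" and "Nonparametric tests were used when the distribution of the data was nonnormal". It names no nonparametric test, does not single out the group-by-time term, and does not mention sex.

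The Study Design section and Table 1 put the gait adaptability test at T0, T1 and T2. The randomization paragraph at the end of the VR Group section stratifies allocation by sex: "Two strata (male and female) will be identified, and randomization will be applied to each stratum". The Sample Size section targets within-between differences with "f=0.2, α=.05, and *P*=.80 were chosen to favor clinically significant effect sizes" and arrives at 50 participants.

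**The concern.** Three features of the stated analysis sit poorly with hypothesis 2.

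- **The answer is not isolated or reported.** A repeated measures ANOVA yields a group effect, a time effect and their interaction. Only the interaction addresses hypothesis 2, and the plan does not say so. The stated follow-up (Tukey) compares cell means, and the stated effect measure (partial η²) has neither sign nor unit. Neither shows how much more VR improved than NW.
- **The question can change after a normality check.** The switch depends on the observed data and leads to tests that are not named. Some common rank tests do not compare improvement between groups.
- **Available information is used less well than it could be.** T0 enters as a level of the time factor rather than as a covariate, and the stratification factor is not in the stated model.

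At stake are precision in a small trial and a clear, signed headline estimate with an interval.

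**Working it through.** **Inputs.** From the Sample Size section: f = 0.2, α = 0.05, power 0.80 and N = 50, hence 25 per group at the 1:1 ratio in Study Design. The article gives neither the number of visits m nor the pre-post correlation ρ behind the 50; both are assumed below and varied.

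**1. The plan's own figure.** For a group-by-time interaction with two groups, λ = f²·N·m/(1−ρ), on (m−1) and (N−2)(m−1) degrees of freedom.

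- m = 2, ρ = 0.5: at N = 50, λ = 0.04·50·2/0.5 = 8.0 and power is 0.79. N = 52 is needed for 0.80.
- m = 3, ρ = 0.4: N = 50 exactly. With m = 3, ρ = 0.5, N = 42.
- A group main effect at m = 2, ρ = 0.5 would need N = 150.

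So 50 fits an interaction calculation (a within-subject time effect gives the same numbers), not a comparison of overall group means.

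**2. Does the interaction test hypothesis 2?** With T0 and T1 it has 1 degree of freedom, and its F equals the squared t for the difference in mean change; a numerical example gave identical values. In simulation (N = 50, ρ = 0.5, a 0.5 SD gain in both arms, no group difference) its type I error was 0.047. With a true 0.8 SD difference, its power was 0.78, against 0.36 for the group main effect. The right term is in the model, but it matters which term is read.

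**3. What the follow-up delivers.** If T2 enters the same ANOVA, the interaction has (2−1)(3−1) = 2 degrees of freedom and does not identify visit or direction. Tukey over 2×3 = 6 cell means gives 6·5/2 = 15 pairs; none is a difference between two changes. Reading within-arm results side by side is no substitute. In the no-difference simulation above, unadjusted paired t tests (a stand-in for within-arm post hoc results) were significant in one arm only in 44% of trials.

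**4. Gain from baseline adjustment.** For two visits an interaction f corresponds to a difference in change D = 4f = 0.8 SD. The variance per participant is 2(1−ρ) for change and 1−ρ² for ANCOVA, a ratio of (1+ρ)/2. With N = 50, λ = (N/4)·D²/variance = 12.5·0.64/variance = 8/variance.

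| ρ (assumed) | Change: λ | Power | ANCOVA: λ | Power | Variance ratio |
|---|---|---|---|---|---|
| 0.3 | 8/1.40 = 5.71 | 0.65 | 8/0.91 = 8.79 | 0.83 | 0.65 |
| 0.5 | 8/1.00 = 8.00 | 0.79 | 8/0.75 = 10.67 | 0.89 | 0.75 |
| 0.7 | 8/0.60 = 13.33 | 0.95 | 8/0.51 = 15.69 | 0.97 | 0.85 |

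Simulation at ρ = 0.5 gave ANCOVA power 0.88 and type I error 0.045. The Abstract gives 40 participants and the Sample Size section recruits 60; at ρ = 0.5 the corresponding gains are 0.69 to 0.81 and 0.86 to 0.94. At N = 50 and ρ = 0.5 the 95% CI half-width falls from 2.01·√(2/25) = 0.57 SD to 0.57·√0.75 = 0.49 SD.

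**5. Sex.** The article gives no association between sex and outcome, so the gain from including it cannot be computed.

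**6. The nonparametric switch.** Nonnormality is plausible for the outcomes of hypothesis 2: the Gait Adaptability Test section scores stepping and crossing as 10 or 5 and counts step adjustments. A Friedman test within a group, or a Mann-Whitney test at one visit, does not compare improvement between groups. A Mann-Whitney test on change scores does. The text does not say which is meant.

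**The case against.** The strongest reply is that the planned ANOVA already contains the hypothesis 2 test, that it is valid, and that the trial was evidently sized for it. That stands. A reader might infer that the analysis cannot test hypothesis 2; the T0/T1 identity above shows otherwise.

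Other strong readings also fail:

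- **That T0 is ignored.** It is used as a time level, and analysis of change is unbiased under randomization. The 0.79 at ρ = 0.5 is essentially the planned 0.80, so baseline adjustment adds precision and does not repair a bias.
- **That a three-visit model with 15 Tukey pairs is planned.** The text speaks only of before and after. T2 is collected, so the reading is possible but not stated.
- **That a failed normality check deletes hypothesis 2.** No nonparametric test is named, and one applied to change scores would preserve it.
- **That Tukey's multiplicity penalty costs power for hypothesis 2.** Tukey is post hoc; the interaction test does not pay that penalty.
- **That a nonsignificant result is to be read as equivalence.** The remark about equivalent or superior improvements is rationale. Hypothesis 2 is a superiority hypothesis, and no equivalence claim is planned.

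A separate analysis plan may also add covariates and intervals, so the absence of sex alone is weak evidence of a fault. What remains is that the method the article does state is less efficient and less direct than its own data allow, and that its rule for nonnormal data does not protect the question.

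**Conclusion.** The point holds as an improvement available at no extra data cost; it is not a finding that the planned test is invalid. The group-by-time term tests hypothesis 2, but it is not named as decisive, its stated follow-up and effect measure do not give the VR-minus-NW difference in improvement, and the switch for nonnormal data may lead to tests that do not address it.

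The measurable part is efficiency. At 25 per group, adjusting T1 for T0 is worth 0.18, 0.10 or 0.02 in power at ρ = 0.3, 0.5 or 0.7. Put differently, if the change analysis had 80% power at N = 50, ANCOVA would need about 34, 40 or 44 in total. These figures rest on the assumed ρ, on the two-visit conversion of f = 0.2 to 0.8 SD, and on equal variances at T0 and T1. The gain shrinks as ρ rises. The case for including sex rests on the stratified design, without a computed gain.

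**What to change.** Amend the Statistical Analysis section before outcome data are examined:

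1. Test hypothesis 2 for the gait adaptability outcome with one planned contrast: VR minus NW at T1, adjusted for the T0 value and sex, by ANCOVA or an equivalent mixed model. Report the estimate with its 95% CI.
2. Give the same contrast at T2 as secondary.
3. Keep this contrast when residuals are nonnormal, using bootstrap or permutation inference (permuting within sex strata), instead of moving to a different test.
4. If Tukey comparisons and partial η² are retained, label them descriptive and state that they do not decide hypothesis 2.

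The cost is a few sentences. No new measurements, visits or participants are needed, because T0 and sex are already recorded.

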## Results

Data collection will begin in September 2025, and the first results are expected in December 2025.

## Discussion

This study aims to compare the effectiveness of 2 gait training programs intended to improve older adults’ gait adaptability behavior. More precisely, the aim is to evidence that VR is the more relevant tool to propose gait training programs for healthy older adults compared with a conventional training program such as NW training.

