##### Precaution 2: Following Motor Learning Principles

According to Hendry et al [45], gait adaptability training program implementation should be based on 4 motor learning principles.

The first principle is related to the variability of practice, which is necessary to optimize the improvement of gait adaptability behavior in older adults. Task variability is crucial for learning optimization by confronting older adults with a large range of potential gait adjustments based on their own gait capacities. In previous studies, older adults were confronted with various environmental lighting conditions [36]; changes in the number, size, and shape of obstacles [35]; and configurations of obstacles [37] with a training progression. Future XR gait training implementation should include the manipulation of variability based, for example, on the modulation of VE spatial constraints (obstacle characteristics and configurations).

The second principle is related to the amount of practice and, more precisely, to task repetitions. Performing any repetitions is a *sine qua non* for optimizing any learning [45]. In previous studies, experimenters provide a very global estimation of the amount of practice, for example, 15 sessions of 60 minutes [36], 18 sessions of 45 minutes [35], and 30 sessions of 40 minutes [37]. However, there is no precise information about the number of repetitions for each task performed. The combination of these first 2 principles underlines the importance of the concept of “repetition without repetition” [46,47]. Future XR gait training implementation should be based on a large amount of practice (task repetition) coupled with a large variability of practice.

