### Gait Training Programs: NW Versus VR

#### Overview

The 2 gait training programs will be dose-matched in terms of duration (ie, 45 min per session) and frequency (ie, 3 sessions per week) of training over a 6-week program (ie, 18 training sessions) following the methodology used in previous gait training studies [35-37]. Previous studies have shown that extensive practice is important for the consolidation and retention of motor memory [68]. Therefore, in line with our ambition to develop long-term improvements in gait adaptability behavior, a large amount of practice in our gait training programs is necessary.

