#### NW Group

In the NW group, participants will practice the training sessions in a nature park. They will be instructed to walk with poles continuously around the park. Each training session will consist of a warm-up period (10 min), main exercise (45 min), and cool-down period (5 min). Participants will adapt their locomotion to uneven terrain. They will negotiate natural obstacles such as avoiding a rock or crossing over a tree root, thus improving their gait adaptability capacities. Sessions will be provided by a coach from a multisport club proposing programs of physical activity adapted to older adults. Participants will follow the coach, who will progressively increase the level of difficulty over the 6 weeks, show the way, and adapt to the gait speed.

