#### VR Group

In the VR group, participants will practice the training sessions in an experimental room. In 1 training session, participants will negotiate 60 trials. Sessions will be provided by the principal investigator. Participants will practice gait training sessions in a fully immersive VR. A wireless HTC Vive Pro VR-HMD will be used to display VE (Figure 2A). Participants will wear HTC Vive Pro foot trackers on their feet, which will record their feet positions (in relation to obstacles) and display 2 virtual foot avatars in the VE. A security system consisting of a safety harness (Figure 2C) connected to an in-ceiling rail by a lanyard (Figure 2B) will provide training sessions in a safe context. This setup has been validated in a previous study [44] in which gait adaptability behavior was similar in the real world and in VR.

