Finally, with greater individualization compared with the NW training and the possibility of offering feedback during training, the VR training should maximize the behavioral and psychological benefits of the training program in older adults.

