### Conclusions

The validation of the hypothesis concerning the greater effectiveness of the VR gait training program compared with the training program of NW should confirm that VR is the more promising tool in fall prevention. In addition, the study of VR-HMD acceptance in a longitudinal way (over a training program) should allow a better understanding of the psychological determinants of the behavioral intention to use technology among older adults to prevent falls. Increasing the effectiveness and acceptance of older adults’ training programs based on XR devices to prevent fall occurrence is a challenge to be met in the face of such a significant health issue.

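### The Discussion and Conclusions credit VR as a tool, but the two arms compare whole programmes that also differ in trainer, progression, feedback and obstacle practice

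*Protocol article*

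**What the plan says.** The article states its purpose at two levels.

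- **Programme level.** Objectives of the Study and Hypotheses predicts that "the VR gait training program will induce greater improvements in gait adaptability capacities in comparison with the NW training (hypothesis 2"). The abstract's objective, the Study Design section and the Statistical Analysis section also refer to two training programmes.
- **Tool level.** The Discussion says that "the aim is to evidence that VR is the more relevant tool to propose gait training programs for healthy older adults"; the sentence goes on to name conventional training such as NW as the comparator. The Conclusions say that validating the superiority hypothesis "should confirm that VR is the more promising tool in fall prevention".

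On matching, the Overview of the training programmes says: "The 2 gait training programs will be dose-matched in terms of duration (ie, 45 min per session) and frequency (ie, 3 sessions per week"). No other feature is said to be matched.

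On content, the VR Group section says "In 1 training session, participants will negotiate 60 trials". The NW Group section says of its participants: "They will negotiate natural obstacles such as avoiding a rock or crossing over a tree root". It gives no number.

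On why VR should do better, the Discussion points to the VR arm's training content, "with greater individualization compared with the NW training and the possibility of offering feedback during training".

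**The concern.** A two-arm trial yields one contrast for each outcome. Here that contrast carries the headset together with everything else that differs between the arms. If the VR arm improves more, the result fits an effect of the medium, but it fits equally well an effect of the trainer, of individual progression, of feedback, of the amount or type of obstacle practice, or of a mixture of these. The article itself names individualisation and feedback as reasons to expect a VR advantage, so it supplies part of the rival explanation.

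At stake is the sentence that readers will carry away. If the plan is followed as written, a positive hypothesis 2 will be reported as evidence that VR is the better tool for gait training and fall prevention, when the evidence would be that one particular package outperformed another. Limitations of This Study covers the population, the fixed equipment and usability, but not this.

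**Working it through.** No figure in the plan needs reproducing, because the point is about attribution and not about sample size or power. The check sets the two arm descriptions side by side.

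| Feature | VR programme | NW programme | Matched? |
|---|---|---|---|
| Nominal duration and frequency (Overview) | 45 min, 3 per week, 6 weeks | the same | stated as matched |
| Trainer (VR Group; NW Group) | principal investigator | multisport-club coach | no |
| Progression (VR Group; NW Group) | 18 levels; a participant moves up only after a successful session; obstacles scaled to leg length | the coach raises difficulty over the six weeks and adjusts to walking speed | no |
| Feedback (VR Group) | result of a trial, if the participant asks for it | not described | not stated |
| Obstacle practice (VR Group; NW Group) | 60 trials per session | natural obstacles, no number set | cannot be judged |

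**Planned practice, VR.** Sessions: 3 per week × 6 weeks = 18. Trials: 18 × 60 = 1,080 per participant at full attendance. A trial may hold more than one obstacle, so this counts trials, not obstacles.

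**Planned practice, NW.** No count is given, so no ratio can be formed. The direction is open too. To meet 60 obstacles in the 45-minute main exercise, a walker would need one every 45 × 60 / 60 = 45 seconds. The article gives nothing by which to judge whether the park route offers more or fewer. The units also differ: a VR trial is not one natural obstacle, and continuous adaptation to uneven ground has no trial count at all.

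**Attribution.** Write the between-arm difference in improvement as D = (effect of the medium) + (joint effect of trainer, progression, feedback and practice, with any interactions). The trial estimates D. No arm delivers the same content without a headset, so the two terms cannot be separated. A larger sample would make D more precise without splitting it.

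**Claim against design.** Hypothesis 2 is a statement about D, so the design supports it. The tool-level sentences in the Discussion and Conclusions are statements about the first term, so it does not support them.

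**A side point on the one matched feature.** The NW Group section describes 10 + 45 + 5 = 60 minutes per session, while the Overview gives 45. The two passages should be reconciled. The argument above does not depend on how.

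**The case against.** The strongest reply is that the trial compares programmes and mostly says so. The objective, hypothesis 2, the design and the analysis are at that level, and randomisation gives a valid test there. This stands: nothing in the hypothesis, outcomes or analysis is invalidated, and a reader who inferred that hypothesis 2 itself is untestable would be wrong.

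A second reply is that individualisation and feedback are what the VR software delivers, and so are part of the tool. This stands in part. Tracker-based scoring and virtual obstacles make both practical in VR, whereas rocks and roots in a park cannot be scaled to leg length. Yet the article's own gait adaptability test uses physical obstacles scaled to leg length and scores performance on them in the real world, so scaling and scoring are not exclusive to a headset. The reply also leaves out the trainer and the uncounted NW practice, neither of which is intrinsic to VR.

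A third reply is that NW was a deliberate comparator, chosen for its ecological context. That is a fair reason to compare programmes. It does not license a conclusion about the medium.

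Some stronger readings are tempting but not supported:

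- *The VR arm gets several times the obstacle practice.* Any such ratio needs an NW count that the article does not give, in a comparable unit.
- *NW participants get no feedback, or their obstacles will go unrecorded.* The article is silent and condensed. Silence is not evidence of absence.
- *The trial repeats the fault it finds in earlier work.* The remark that "there is no precise information about the number of repetitions for each task performed" is aimed at earlier extended-reality programmes, and this trial does set a number of trials for its own VR arm.
- *VR is individual coaching and NW is a group class.* Neither format is described in those terms.

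**Conclusion.** The concern holds as a limit on interpretation. The design can show that this VR programme improves gait adaptability more than this NW programme. It cannot show that VR is the more relevant or more promising tool, because the medium is bundled with trainer, progression, feedback and obstacle practice, and only duration and frequency are stated to be matched.

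The one quantity available is the VR arm's 1,080 planned trials, which assumes full attendance. The NW equivalent is unknown, so the difference in repetitions has neither a size nor a sign. The conclusion does not need one: it rests on the arm descriptions as published, on there being two arms only, and on no arm giving the VR content without a headset. The trainer difference alone would be enough to block the tool-level claim.

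**What to change.** 1. In the Discussion and the Conclusions, replace the tool-level claim with the comparison actually made, for example: *this individualised VR obstacle-training programme with feedback versus this coach-led Nordic walking programme*.
2. In Limitations of This Study, list the bundled differences (trainer, progression, feedback, obstacle practice), giving most weight to trainer and unmatched practice, and say that a difference between arms cannot be assigned to any one of them.
3. Optionally, have the coach who already leads the sessions record an approximate obstacle count per session, and report it descriptively beside the hypothesis 2 result. It has to be arranged before training starts, and it will be rough because the coach is also leading the walk. It would describe practice in the NW arm but would not separate the components.

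Steps 1 and 2 cost only wording and a narrower claim. Step 3 adds a small recording task. None of them changes the arms, the sample size or the analysis.
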